#### Where

Owing to the long distances between the VITALISE Living Labs and the COVID-19 pandemic situation, all interviews and workshops will be arranged on the web using Microsoft Teams, Google Meets, or Zoom videoconferencing platforms. If the COVID-19 pandemic situation allows, face-to-face workshops will be organized as a part of the VITALISE project consortium meetings during phase 3.

#### When and How Much

During phase 1, each Living Lab’s internal workshop where they collectively discuss and refine their existing Living Lab practice responses will occur once and is expected to take approximately 3 hours. If the time is not sufficient, Living Labs will be encouraged to keep as many workshops as required to properly fill the Microsoft Excel templates. Living Lab interviews focusing on deepening the understanding regarding each Living Lab’s current practice will occur once and is expected to last approximately 2 to 2.5 hours. Living Lab interviews that focus on evaluating the key experiences regarding the case studies from the Living Lab operator's point of view will also occur once and are expected to last approximately 2 to 2.5 hours each. It is estimated that at least three (web-based) workshops with an estimated 3-hour duration each are needed to agree on the harmonized research protocols for developing big data–driven personas. After each workshop, a web-based voting procedure will be conducted to evaluate the consensus among Living Labs and harmonization bodies. The proposed research protocols will be modified until the voters reach a supermajority agreement (ie, at least a 70% acceptance rate). If an agreement is not reached during the first 5 iterations, the process will end, and disagreements regarding the research protocol and included technologies, methods, tools, and other scientific instruments will be documented.

#### Tailoring and Modifications

In principle, interviews and workshop interventions follow the same principles for all participants, and modifications are not preplanned. However, if a need to make modifications emerge, they can be made.

### Case Study Interventions for Phase 2

#### Case Study 1: Digital Coaching App Impact on Self-efficacy and Well-being

##### Why

The general aim of this case study is to test the digital coach app of the Austrian Institute of Technology (AIT) by analyzing to what extent it can influence individuals’ self-efficacy and well-being by motivating older adults to practice a healthy lifestyle. Moreover, the study will also assess the system’s usability, learnability, and user acceptance. The monitoring of the effects of the coach app use may throw light on the capability of digital coaching in helping retirees maintain (and improve) social relationships and activities that could be put at risk by their withdrawal from the workplace. The study evaluations will be set up in 2 different sites: Belgium and Austria. This multisite design will allow the evaluation of the AIT coach app in different social and cultural contexts.

##### To Whom (Sample Size and Recruitment)

A total of 40 persons will be recruited via the AIT (Austria) and LiCalab (Belgium) user panel databases. Social media channels and collaborations with local authorities will also be used. Key inclusion criteria include the following: for group A, older employees in good health (maximum approximately 3 years before retirement; work continuity during the study), and for group B, retired older people (retired for no longer than 3 years). For both groups, the availability of smartphones (Android version 8.0 or up, or iOS) was a key inclusion criterion. Key exclusion criteria include age <55 years and middle-to-severe constraints in mobility or cognition (self-assessed). For group B, care dependency (self-assessed) is also an exclusion criterion.

##### What (Materials)

Within the study, AIT’s digital coaching app will be provided to the participants. The software used for the trials comprises a smartphone-based app and a server component providing the content and collecting the data. Communication between the front-end and back-end is established over the internet using secure communication channels. The back-end server runs within the facilities of the AIT’s partner organization, ProSelf, to ensure privacy and security. No personal data will be stored in the cloud. A paper user manual will be provided to the participants to guide them through the first steps of installing, configuring, and using the app. Informed consent will be provided in paper form; questionnaires for collecting quantitative data will either be provided in paper form or as a link to a web-based questionnaire.

##### What (Procedures)

The study will follow a mixed methods design in which qualitative and quantitative data will be collected. To determine the effects of AIT’s digital coaching on the 8-week term, 2 measurements (time point 0 [T0] and time point 1 [T1]) will be conducted using standardized tests. Thus, 2 face-to-face sessions will be scheduled with participants: 1 just before the beginning of the study and 1 at the end, after 8 weeks of use. Both qualitative and quantitative outcomes will be measured. At baseline (T0, before the start of the intervention), demographic data will be collected. The following outcomes will also be measured both at baseline (T0) and after the end of the intervention (T1): patient-reported outcome measures, including health and well-being (Short Form-36 version 2) and social life (Lubben scale), self-efficacy (General Self-Efficacy Scale-6), and patient-reported experience measures including, UX (User Experience Questionnaire [UEQ]) and basic health measures (eg, weight).

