##### How

Within the study, AIT’s digital coaching app will be provided to the participants. Participants will be provided with a link to install the app on their own smartphones. The app will be provided individually to all participants in the study.

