### Case Study Outcomes

#### Case Study 1

This study will allow a better understanding of how digital coaching can influence individuals’ well-being and social participation by motivating older adults to practice a healthy lifestyle. Monitoring the effects of AIT’s digital coaching app use may shed light on the capability of a digital coach for helping retirees maintain (and improve) social relationships and activities that could be put at risk by their withdrawal from the workplace. In addition, the results will also allow the optimization of the UX of deployed coaching mobile apps. By setting up this case study at 2 different sites, Belgium and Austria, specific results related to these different social and cultural contexts are also expected.

#### Case Study 2

The results of the randomized controlled trial will show that it is feasible to conduct a randomized controlled trial of yoga in a virtual and sensor-assisted Living Lab environment using the described protocol. Moreover, the collection of novel sensor data from the experiment is expected to provide insightful information about the physical and psychological status of the participants.

#### Case Study 3

The results of this study will allow the analysis of effectiveness, usability, and acceptance of the described Gradior Active intervention. It will state the pillars for evidence-based decision-making on investment in the upgrade and modernization of the prototype; at the same time, it will ensure a final co-design sprint with participants to orient the incremental development plans.

#### Case Study 4

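### Case study 1 sets out to determine the effects of the coaching app, but everyone receives it and only a before-after comparison is planned, so change cannot be attributed to the app

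*Protocol article*

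**What the plan says.** All of this is in the protocol article, under Case Study 1 unless stated otherwise.

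- **Heading and Why.** The heading speaks of the app's impact on self-efficacy and well-being. The general aim is to test the app by "analyzing to what extent it can influence individuals’ self-efficacy and well-being by motivating older adults to practice a healthy lifestyle". Usability, learnability and user acceptance are further aims.
- **What (Procedures).** The measurements are introduced with "To determine the effects of AIT’s digital coaching on the 8-week term, 2 measurements", namely T0 and T1. The two sessions are "1 just before the beginning of the study and 1 at the end, after 8 weeks of use". The outcomes include the Short Form-36 version 2, the Lubben scale and the General Self-Efficacy Scale-6.
- **How.** "The app will be provided individually to all participants in the study".
- **To Whom.** "A total of 40 persons will be recruited via the AIT (Austria) and LiCalab (Belgium) user panel databases". Group A is older employees at most about 3 years from retirement who keep working during the study. Group B is people retired for no more than 3 years.
- **Data Analysis Plans for Case Studies During Phase 2.** Case studies that evaluate an intervention's impact have one measurement before and one after. Paired and unpaired tests appear in a general list that is not assigned to individual case studies.
- **Case Study Outcomes.** "This study will allow a better understanding of how digital coaching can influence individuals’ well-being and social participation".

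**The concern.** The objective is worded as a causal one (impact, effects, influence), but the design yields only change over time. For case study 1 the article describes no randomisation, app-free group, waiting list or repeated baseline. What participants would have scored at week 8 without the app is therefore neither observed nor approximated.

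The gap matters for these outcomes. The well-being, social-life and self-efficacy scales are self-reported. Participants are volunteers who, according to the Incentives section, are offered a programme meant to improve well-being and social participation, so expectation can move the answers. Group B has recently retired and may still be adjusting. Elsewhere the article anticipates COVID-19 restrictions, which bear directly on social life. If the objective stands as written, a significant T0 to T1 difference invites a conclusion about the app that the data cannot carry.

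**Working it through.** The article gives no power calculation or effect size for case study 1, so there is no figure to reproduce. The check is to set the stated objective against each contrast the design offers.

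**Possible contrasts**

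| Contrast | What differs | Identifies the app's effect? |
|---|---|---|
| T0 against T1, same people | App use, and also 8 weeks of time, season, external events, repeat testing and expectation | No |
| Group A against group B | Retirement status; both groups have the app | No. At most it shows whether change differs by retirement status |
| Austria against Belgium | Site and culture; both sites have the app | No. At most it shows whether change differs by site |

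No contrast sets app use against no app use, so the effect named under What (Procedures) is not estimable without assuming that nothing else moved the scores.

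**Comparison with case study 3.** That study introduces its T0 and T1 measurements with nearly the same effect wording. Its How section, however, says that the format is quasi-experimental, has no control group and uses each participant as their own control. Case study 1 has the same structure and no such statement.

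**Illustration of what a significant paired test would mean.** The documents give n = 40. The other inputs are assumptions, not estimates: a true app effect of zero, a non-specific drift d between T0 and T1 of 0 to 0.5 SD, a T0–T1 correlation r of 0.5 or 0.7, and no dropout. The standardised paired difference is d / √(2(1 − r)), and the noncentrality is that value times √40. For d = 0.3:

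- r = 0.5: 0.3 / √1.0 = 0.30, and 0.30 × 6.32 = 1.90
- r = 0.7: 0.3 / √0.6 = 0.387, and 0.387 × 6.32 = 2.45

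Probability that a two-sided 5% paired t test is significant:

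| Drift d (SD) | r = 0.5 | r = 0.7 |
|---|---|---|
| 0 | 0.05 | 0.05 |
| 0.1 | 0.10 | 0.13 |
| 0.2 | 0.24 | 0.36 |
| 0.3 | 0.46 | 0.67 |
| 0.4 | 0.69 | 0.89 |
| 0.5 | 0.87 | 0.98 |

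The test is two-sided, so these probabilities are the same for drift in either direction. The table shows only that the paired test has its nominal error rate for an app effect when drift is exactly zero. It does not say how much drift to expect.

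**The case against.** The strongest reply is that this is a small-scale case study. The project's main aim is a harmonised research protocol, and the case studies exist largely to try out methods and tools. An uncontrolled before-after design is a common and openly described choice for that purpose, and usability and acceptance need no control group. The wording is also partly hedged: Why and Case Study Outcomes say that monitoring the app may be informative about what digital coaching can do, and the analysis section describes the tests as looking for possible findings and future directions. A journal article may also leave its discussion of limitations to a fuller document.

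Much of this stands, and it limits the weight of the point. It does not remove it. The procedures section gives determining effects as the purpose of the measurements, and the heading and aim point the same way. Giving the app to everyone is a stated design feature, not an omission through condensing.

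A reader might go further in three ways that the documents do not support:

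- **That the bias flatters the app by a calculable amount, for example through regression to the mean.** Eligibility has no low-score criterion. Group A must be in good health, and care dependency is excluded in group B. Selection could push either way.
- **That a significant result will be reported as an app effect.** This is a prediction; the hedged passages leave room for a careful report.
- **That the study must be redesigned with a randomised comparison.** The usability, acceptance and descriptive aims can be met as the study stands.

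**Conclusion.** The point holds as a mismatch between objective and design. Case study 1 can estimate change over 8 weeks of app use, but not the effect of the app. This follows from the stated design alone and needs no numerical assumption. The size and direction of the error in reading change as effect cannot be derived from the documents, and the drift table above is illustrative only. The usability, learnability and acceptance aims are unaffected. The matter should be corrected because it governs what the study may conclude, but it does not stand in the way of running it.

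**What to change.** Reword four places in Case Study 1: the heading, the aim under Why, the opening of What (Procedures), and the entry under Case Study Outcomes. They should say that the study:

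- estimates the change from T0 to T1 over 8 weeks of app use, with 95% confidence intervals, by group;
- assesses usability, learnability and acceptance;
- has no control group, and does not attribute change to the app.

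Case study 3's How section is a model for disclosing the lack of a control group.

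The cost is wording only. Recruitment, visits and measurements stay as they are. The price is a less favourable claim, since the study would no longer promise to determine effects.

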##### What (Procedures)

The study follows a mixed methods design in which qualitative and quantitative data will be collected. To determine the effects of Gradior Active on the 8-week term, 2 measurements (T0 and T1) will be conducted using standardized tests. Thus, 2 face-to-face sessions will be scheduled with participants: 1 just before the beginning of the study and 1 at the end after 8 weeks of use. At baseline (T0, before the start of the intervention), demographic data will be collected. The following outcomes will also be measured both at baseline (T0) and after the end of the intervention (T1): patient-reported outcome measures, including health and well-being (Short Form-36 version 2), social life (Lubben scale), Geriatric Depression Scale (GDS), Physical Status Scale (Rapid Assessment of Physical Activity), and (4) Borg Scale of Perceived Exertion; and patient-reported experience measures, including UX (UEQ) and usability and acceptance (System Usability Scale).

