##### To Whom (Sample Size and Recruitment)

In Finland, the sample group will comprise older adults aged >67 years. To recruit older adults with varying physical fitness levels, the following strategy will be applied: open calls to promote free of charge physical fitness level measurement as part of a research project will be published in local newspapers and social media channels in collaboration with the local city administration responsible for older adult services. Furthermore, the collaboration will be conducted with selected nursing home administrators to recruit participants with weaker physical fitness levels directly from nursing homes. It is estimated that approximately 200 to 400 persons will be recruited via open calls and approximately 50 persons from nursing homes. In Hungary, the sample group will comprise people aged >55 years. Social media, posters in outdoor trails and fitness parks, former contact lists, and snowball sampling will be used to recruit the participants. It is estimated that 30 to 50 persons will be recruited; however, because of dropouts during the training program, only 20 are expected to take part in the posttest. In Spain, the main target sample will be men and women aged between 60 and 80 years. of Participants will be recruited in collaboration with the city council of Gernika-Lumo, local nursing homes, and retiree associations. It is estimated that 20 to 40 people will be recruited from all collaborative organizations.

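### Case studies 1 and 3 score user acceptance only at a session placed after 8 weeks of use, so people who stop early may be missing from the result

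*Protocol article*

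**What the plan says.** **Aim.** In Case Study 1, Why, "the study will also assess the system’s usability, learnability, and user acceptance". Case Study 3, Why, sets the same three properties and the overall experience as its general aim.

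**Sample.** In Case Study 1, To Whom, "A total of 40 persons will be recruited". Case Study 3 recruits 30. Neither gives a dropout figure.

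**Timing.** Case Study 1, What (Procedures), says that "2 face-to-face sessions will be scheduled with participants" and places them as "1 just before the beginning of the study and 1 at the end, after 8 weeks of use". Case Study 3, What (Procedures), has "1 just before the beginning of the study and 1 at the end after 8 weeks of use". Both sections also describe T1 as following the end of the intervention.

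**Instruments.** Case 1 lists the UEQ at T0 and T1, under experience measures. Case 3 lists the UEQ, and the System Usability Scale for usability and acceptance, also at T0 and T1.

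**Other sources.** Both products have "a server component providing the content and collecting the data" (What (Materials) in each case study). Case 3 adds UX diaries (What (Materials)), UX collection during the 8-week test (How), and two cocreation sessions for the people who tested the prototype (When and How Much). The Phase 2 section mentions a UX survey with questions harmonised across case studies, but does not say when it is given.

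**The concern.** In a test of a product, stopping because it is tiresome, confusing or useless is evidence on acceptance. If the acceptance score comes from one session after 8 weeks of use, someone who deletes the app in week 2 may give no score, and the plan has no other outcome in which the stopping would show. It would then appear only as a missing questionnaire.

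The scores from those who remain would tend to look better than the product deserves, and the reasons for giving up would go unrecorded. Those reasons matter for redesign and for the personas that the project wants to build. Case Study 3 under Case Study Outcomes also says its results will support decisions on investing in an upgrade of the prototype.

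The point concerns the acceptance aim only. It is separate from whether a before-after change in health can be attributed to the product.

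**Working it through.** The article gives no sample-size calculation, dropout rate or acceptance proportion for these two case studies, so there is no figure of its own to reproduce. The check is mainly a reading of the text.

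**Step 1. Which scores can reflect use?** The UEQ and System Usability Scale are taken at T0 and T1. T0 precedes any use, so only T1 can carry experience with the product.

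**Step 2. Who is measured at T1?** Two wordings stand together. One ties the session to 8 weeks of use. The other schedules it with participants, after the end of the intervention. The first suggests people who used the product throughout; the second suggests everyone at a calendar time. The article does not settle which applies to someone who has stopped.

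**Step 3. How does the consortium treat dropouts elsewhere?** For the Hungarian 8-week programme in case study 4 (To Whom), 30 to 50 are recruited but "because of dropouts during the training program, only 20 are expected to take part in the posttest". There, leaving the programme is expected to mean absence from the posttest. The implied loss is:
- 1 − 20/30 = 33%
- 1 − 20/50 = 60%

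Applied to cases 1 and 3, purely as an assumption, T1 would hold:
- case 1: 40 × (1 − 0.33) ≈ 27, down to 40 × (1 − 0.60) = 16
- case 3: 30 × (1 − 0.33) ≈ 20, down to 30 × (1 − 0.60) = 12

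**Step 4. What else would record a stop?**

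| Source | Case 1 | Case 3 |
|---|---|---|
| Questionnaire at stopping | not described | not described |
| Use or discontinuation as an outcome | not named | not named |
| Diaries or UX during the 8 weeks | not described | yes |
| Group sessions for testers | not described | yes, no completion condition stated |
| Server data | collected, use not named | collected, use not named |

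**Step 5. Direction and possible size.** Let d be the share who stop and are not measured, p the acceptance among those measured, and s the acceptance among those who stopped. Acceptance over all starters is (1 − d)p + ds, so the measured value exceeds it by d(p − s). The excess is positive whenever people who stopped are less accepting. With p = 80% assumed:

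| d | s = 0% | s = 40% |
|---|---|---|
| 10% | 72% | 76% |
| 20% | 64% | 72% |
| 33% | 53% | 67% |
| 60% | 32% | 56% |

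For example, at d = 20% and s = 40%: 0.80 × 0.80 + 0.20 × 0.40 = 0.72. Every p and s here is invented for illustration. The plan defines no acceptance proportion; its questionnaires are to be summarised by means, frequencies and SDs. The table shows how the result depends on d and s, not what it will be.

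**The case against.** The strongest reply is that nobody is excluded. The sessions are scheduled with participants, T1 follows the end of the intervention, and 8 weeks of use can be read as the length of the period. On that reading someone who stopped in week 2 is still invited in week 8. A reader might infer that the plan leaves such people out by design. The documents do not support that, because no rule says so. What remains is that no rule says they will be assessed either, and the case study 4 text shows that dropouts are expected to miss a posttest.

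The second reply concerns case 3. Diaries, UX collected during the test, and individual supervised sessions could capture experience up to stopping and the reasons for it. The cocreation invitation already goes to those who tested the prototype, with no condition of completion. This stands and narrows the point for case 3. These sources are not described as giving a UEQ or System Usability Scale score, and the latter is the instrument named for acceptance. In case 1 no such sources are described.

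Third, stopping is not always a verdict on the product. Case Study 3, Tailoring, itself mentions availability and transport. This stands too: only product-related stopping should be read as non-acceptance.

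Fourth, an article may leave missing-data handling and detailed definitions to the full protocol or analysis plan. That is right for methods of analysis. It does not answer a gap in collection, because no analysis can recover a score or a reason that was not asked for at the time.

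Finally, case 1 labels the UEQ as user experience and names no separate acceptance instrument, so treating it as the acceptance score is partly a reading of the text.

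**Conclusion.** The point holds as a risk that the wording leaves open. It is not a demonstrated bias. In both case studies acceptance is an aim, and the standardised scores that can reflect use come from one session worded as following 8 weeks of use. No assessment at stopping is described, and no use or discontinuation outcome is named. People who stop early may therefore be missing, and the result would then lean towards continuing users. The gap is clearest in case 1 and smaller in case 3.

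The size cannot be computed from the article. The 33–60% loss belongs to an outdoor training programme in another case study. It may not carry over to a home app or to supervised clinic sessions. The direction rests on one assumption: that people who stop are on average less accepting than those who continue.

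**What to change.** 1. State in both case studies that T1 is sought 8 weeks after T0 from every participant who started, whether or not still using the product.
2. When someone stops, offer the UEQ (and in case 3 the System Usability Scale) with one question on the reason. The paper or web form already planned can carry it.
3. Report beside the questionnaire scores the share of starters still using the product at week 8 and, in case 3, sessions completed out of 2 × 8 = 16, from server or session records. Show product-related stopping as non-acceptance, and other reasons separately.
4. In case 3, confirm that the cocreation invitation includes testers who stopped early, as its wording already allows.

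**Cost.** A few sentences of protocol text, one added question and a summary of stored records, with no new visit or device. Some scores will come from people with short exposure, so time of use should be reported with them. It must first be confirmed that the server logs use in enough detail; the article says only that it collects data. The change has to come before data collection, because stopping reasons cannot be reliably collected afterwards.

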The *main quantitative analysis approaches* will include descriptive data (eg, mean, frequency, and SD) to characterize the participants’ (sociodemographic variables) and summarize the results of the questionnaires. Chi-square tests will be used to detect the associations between the categorical variables when needed. To explore whether the outcomes of the interventions are significant, parametric (eg, paired and unpaired 2-tailed *t* tests, Pearson correlation, and 1-way analysis of variance) and nonparametric tests (Wilcoxon signed-rank test, Mann–Whitney *U* test, Spearman correlation, and Kruskal–Wallis test) will be conducted to investigate the possible research findings and future research directions. Case studies evaluating the impact of the intervention will include 2 temporal data collection moments, 1 before and 1 after the intervention period, to validate the changes that might occur. Standardized statistical tools will be used for data analysis, such as SPSS (IBM Corp) and Microsoft Excel. Sensor data analysis will be used by the sensor device–related software features, for example, for eye-tracking data or wearable sensor temporal activity data analysis, when case studies use them for data collection. The main quantitative analysis approaches include the inductive qualitative content analysis executed in phases 1 and 3. For case study 5, hermeneutic analysis of the phenomenon and content analysis of the photos will also be performed. For all cases, answers to the questionnaires will be extracted and triangulated with quantitative data.

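### Case study 3 schedules the UEQ and System Usability Scale, and case study 1 the UEQ, at T0, before any described use of the product, so those T0 scores can reflect only expectations

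*Protocol article*

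**What the plan says.** **Timing.** Case Study 1, What (Procedures), places T0 ahead of the intervention: "At baseline (T0, before the start of the intervention), demographic data will be collected". Its two face-to-face sessions are "1 just before the beginning of the study and 1 at the end, after 8 weeks of use". Case Study 3, What (Procedures), defines T0 in the same way and has the same two-session structure. Both sections give the purpose of the two measurements as determining the effects of the product over the 8-week term.

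**Outcome lists.** Both sections then state: "The following outcomes will also be measured both at baseline (T0) and after the end of the intervention (T1".
- In case study 1 the list includes "patient-reported experience measures including, UX (User Experience Questionnaire [UEQ]) and basic health measures (eg, weight".
- In case study 3 it includes the "Borg Scale of Perceived Exertion" and "patient-reported experience measures, including UX (UEQ) and usability and acceptance (System Usability Scale".

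**Analysis.** Data Analysis Plans for Case Studies During Phase 2 says that case studies evaluating the impact of an intervention "will include 2 temporal data collection moments, 1 before and 1 after the intervention period", in order to examine change. Case Study 3, How, describes a design without a control group in which each participant serves as their own control.

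**The concern.** The UEQ and the System Usability Scale ask for a rating of a product the respondent has used. At T0 the participant has, on the plan's own description, used nothing. A score recorded then measures anticipation.

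This matters because usability, learnability, acceptance and overall experience are the general aim of case study 3 and an additional aim of case study 1. If T0 and T1 are paired for these scales, as the general analysis text invites, the difference depends on prior expectation as well as on the product. A good product that people expected to be good would show no change. A mediocre one that people expected to be poor would appear to improve.

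**Working it through.** No sample size, power or effect figure is given for these case studies, so there is none to reproduce. The check sets the timing, the lists and the analysis text side by side.

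**1. Is there any product use before T0?**
- Case study 1: T0 precedes the intervention. The How section says participants receive a link to install the app on their own phones, and the When and How Much section gives 8 weeks of app provision between the two sessions. No demonstration or trial use at T0 is mentioned.
- Case study 3: T0 precedes the intervention. The How section says that experience with the prototype is collected during the 8-week testing period. No demonstration, trial session or exertion task at T0 is mentioned.

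**2. Which listed outcomes need something to rate?**

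| Outcome | Case study | Needs prior use or effort? | Object described at T0? |
|---|---|---|---|
| UEQ | 1 | Yes, product | No |
| UEQ | 3 | Yes, product | No |
| System Usability Scale | 3 | Yes, product | No |
| Borg scale | 3 | Yes, an effort | Task not stated at T0 or T1 |
| SF-36v2, Lubben scale | 1 and 3 | No | Valid at baseline |
| General Self-Efficacy Scale-6, weight | 1 | No | Valid at baseline |
| Geriatric Depression Scale, Rapid Assessment of Physical Activity | 3 | No | Valid at baseline |

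**3. Does any text restrict these scales to T1?** No. The T0-and-T1 sentence governs the whole list in both case studies.

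**4. How does the plan time the UEQ elsewhere?** In case study 4 (What (Materials), What (Procedures) and How) participants complete it after finishing the measurement track, that is, after exposure.

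**5. How many records are affected?** Planned samples are 40 (case study 1) and 30 (case study 3).
- Participants: 40 + 30 = 70.
- T0 forms on the two product scales: 40 × 1 (UEQ) + 30 × 2 (UEQ and System Usability Scale) = 100.

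**6. What would a difference mean?** Write T1 = experience and T0 = expectation, so T1 − T0 = experience − expectation. The following values are assumed purely for illustration; the plan gives none. Hold mean experience at +1.0 on the UEQ:
- expectation 0: difference = 1.0 − 0 = +1.0
- expectation +1.0: difference = 1.0 − 1.0 = 0
- expectation +2.0: difference = 1.0 − 2.0 = −1.0

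The same product experience would be read as improvement, no change or decline.

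**The case against.** The strongest reply is that no change analysis is specified for these scales. The analysis section provides descriptive statistics to summarise questionnaires, and its before/after sentence names no instrument. Most of the T0/T1 list consists of outcomes for which a baseline is proper, so the experience scales may have been swept into one long sentence. This stands in part: a reader might infer that the plan commits to a UEQ or usability change score, and it does not say so. It does, however, schedule the scales at both times, under a stated purpose of determining effects, and offers no other use for the T0 values.

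Second, the user-experience aims are not lost. T1 scores follow 8 weeks of use and are sound. Case study 3 also has user-experience diaries and two cocreation sessions with the same participants. This stands in full.

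Third, a Borg rating at T0 could be meaningful if tied to a standard task. This also stands. The article does not name the task, so the supportable criticism is an unstated reference task, not a meaningless measurement.

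Fourth, the article is condensed, and detail may sit in a fuller protocol. That could cover the Borg task. It does not cover the timing of the UEQ and System Usability Scale, which the article states outright.

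**Conclusion.** The point holds for three instrument-by-study pairs: the UEQ in case studies 1 and 3, and the System Usability Scale in case study 3. Following the written schedule would produce T0 scores that can reflect only expectations for all 70 planned participants, and any T0-T1 difference on them could not be read as a product effect. This rests on two assumptions: that participants have not already used the app or prototype (prior use is not mentioned), and that no demonstration takes place at T0 (none is described).

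Three stronger readings are not supported:
- that both case studies collect usability and exertion scales at T0, since case study 1 lists only the UEQ among these;
- that the Borg rating at T0 has no meaning, since its task is simply not named;
- that the user-experience findings of either case study are invalid, since the T1 data remain usable.

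The point is firmest in case study 3, where user experience is the general aim.

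**What to change.** 1. In Case Study 1 and Case Study 3, What (Procedures), remove the UEQ from the T0 list; in case study 3, also remove the System Usability Scale. Collect both only after use.
2. Report the T1 score with a 95% CI as the user-experience or usability result.
3. State in the analysis section that these scales are excluded from the T0-T1 change analysis. The remaining T0/T1 outcomes, apart from the Borg scale (item 4), stay as they are.
4. For the Borg scale in case study 3, name the exertion task it refers to at each time point, or drop it from T0.

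The cost is a few words of protocol text and fewer forms at baseline. It also brings the UEQ timing into line with case study 4. According to the Results section, ethics materials were still being prepared and recruitment had not begun, so on that status the change precedes data collection.

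Optional: if the teams want an early-use score, for example to inform learnability, add one administration after first use. This costs one extra form per participant in each case study and is not needed to correct the problem.
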